#### Laboratory analyses

Sputum samples will be collected from enrolled participants for GeneXpert MTB/RIF analysis. Participants with a positive GeneXpert MTB/RIF rifampicin resistant result will be sent to UNAM biosafety level 3 laboratory for culture and drug sensitivity testing. We will collect blood samples for C reactive protein tests and interferon gamma release assays to evaluate latent TB infection. We will have access to a mobile X-ray facility to take participants’ chest X-rays; we will also include chest ultrasounds. HIV rapid tests will be conducted in the field. Positive results from any test will be formally communicated and followed up with the health service providers in the area ensuring that treatment and/or care is initiated.

#### Data management and analysis

Data from the qualitative and quantitative components of the feasibility study will be stored in separate databases. Qualitative data will be captured and analysed with ATLAS.ti using Attride-Stirling’s framework for thematic analysis to determine acceptability.^15^ Feasibility will be determined by collecting data on recruitment and retention, time required to recruit a participant, number of eligible participants required to recruit required sample size and feasibility of testing procedures and data collection methods.^16^ Yield will be determined by using a number-needed-to-screen approach for each strategy.^17^ Cost will be determined using the incremental cost-effectiveness ratio (ICER) for each case finding intervention strategy.^18^

### Objective 3

#### Epidemiological modelling

Modelling will be carried out, premised on data from objectives 1 and 2. Data from objectives 1 and 2 will be used for the construction of a compartmental transmission model calibrated against Namibian data (Census, Demographic and Health Survey, as well as data describing the TB and HIV prevalence, MDR-TB prevalence, TB/MDR-TB case detection and treatment outcomes) that will not only evaluate the MDR-TB epidemic in Namibia but will also investigate the impact of case finding interventions on MDR-TB incidence. In a base scenario, the status quo will be evaluated, assuming no active case finding. Each of the three interventions will then be evaluated and their impact determined though divergence from the base.

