## Introduction

Namibia is classified by the WHO as a high tuberculosis (TB)-burden country and, in 2020, the TB incidence was estimated to be 460/100 000, with 12 000 new cases/year.^1^ The most recent nationwide anti-TB drug resistance survey in Namibia was completed in 2015, reporting a prevalence of multidrug-resistant (MDR)-TB at 4.5% among new cases and 7.9% among previously treated cases. Approximately 46.6% of patients with MDR-TB were coinfected with HIV.^2^ Based on that prevalence, the number of MDR-TB cases/year is estimated to be around 800. Only 213 cases were detected in 2020.

Namibia faces significant challenges at every step along the TB care cascade, from preventive therapy to diagnostics and patient treatment. Challenges also exist in the identification of prevalent cases of TB infection and disease through passive and active case finding intervention strategies.^3^ During the COVID-19 pandemic, Namibia observed an increased number of missed or undiagnosed TB cases with case management interruptions due to the diagnostic supply chain, redirections of resources and the effects of human movement restrictions, negatively impacting care-seeking.^4^

In the ‘hotspots, hospitals, and households’ (H3TB) study, we aim to identify MDR-TB transmission clusters, through genomic, geospatial and social data interferences, which could indicate transmission hotspots. We aim to determine the diagnostic yield of targeting these areas for active case finding as well as evaluating the cost-effectiveness of such approaches. Our central hypothesis is that geographical heterogeneity in the concentration of genotypes exists within the MDR-TB epidemic in Namibia leading to high-transmission areas (hotspots), where MDR-TB incidence could be up to three times that of the baseline population. Further, if these areas could be identified and targeted through enhanced case finding strategies, these strategies might be more effective than screening and treatment programmes which do not adapt to spatial and biological variation.^5^ In addition to targeting transmission hotspots, our focus will be on MDR-TB screening of household contacts of MDR-TB cases and visitors of hospitalised patients with MDR-TB.

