#### Participant identification

Individuals with a positive Xpert MTB/RIF result with rifampicin resistance demonstrated, and a positive *Mycobacterium tuberculosis* culture, will be included from the three regions. To identify transmission hotspots, whole genome sequencing (WGS) results will be combined with clinical, epidemiological, geospatial and social network data. A traditional sample size calculation is not indicated if most of the MDR-TB cases in a region are included (>80%).^5 6^ In this study, we might miss some MDR-TB cases who are not reported or diagnosed. However, a current surveillance study which started in January 2020 and is ongoing could inform on additional participants from these areas. We will look at other strategies, like including participants from other regions or finding additional cases through collaborating with the NTLP’s active case finding interventions, to ensure robustness of our data.

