#### Health economic modelling

During the feasibility studies, costing data will be collected from each site in a standardised way. Decision analysis will be carried out using the ICER tool. The primary outcome will be the ICER, comparing the three case finding strategies with the baseline scenario, from the societal perspective over a lifetime analytical horizon. One-way sensitivity analyses will be conducted on all model parameters, multiway sensitivity analyses on parameters most critical to the cost-effectiveness estimate, and a probabilistic uncertainty analysis where all parameters are varied simultaneously over distributions to construct 95% uncertainty ranges and cost-effectiveness acceptability curves.

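### The model's base scenario is called the status quo but excludes the active case finding that the national programme already runs, so neither the impact estimates nor the primary ICER would be increments over current practice

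*Protocol article*

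**What the plan says.** Under Objective 3, Epidemiological modelling, the protocol article fixes the comparator: "In a base scenario, the status quo will be evaluated, assuming no active case finding". The next sentence makes it the reference for all effects: "Each of the three interventions will then be evaluated and their impact determined though divergence from the base". The same section calibrates the model to Namibian data, including observed detection of TB and MDR-TB.

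Health economic modelling uses the same reference: "The primary outcome will be the ICER, comparing the three case finding strategies with the baseline scenario". The sensitivity analyses described there vary model parameters singly, in combination and probabilistically. No alternative comparator is stated.

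Two other places describe current activity. Objective 1, Participant identification, lists among its ways to enlarge the sample "finding additional cases through collaborating with the NTLP’s active case finding interventions". The Introduction, describing the present situation in Namibia, says: "Challenges also exist in the identification of prevalent cases of TB infection and disease through passive and active case finding intervention strategies".

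**The concern.** If the national programme already does active case finding, a base without it is not the status quo. The calibration target makes this harder to resolve: observed detection contains any cases found actively, so a base fitted to it does not match its own description.

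The programme is the intended user of the results. Its question is what each strategy would add to what it does now, at what extra cost. A comparator that leaves out existing activity answers a different question, and the error would carry into every impact estimate and into the primary economic outcome.

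**Working it through.** **1. The statements side by side.** The base is (a) the status quo, (b) free of active case finding, and (c) part of a model calibrated to observed detection. Participant identification treats the programme's active case finding as something that exists and can be drawn on. Given that, (a) and (b) cannot both be true, and (b) and (c) agree only if the programme's active yield is nil.

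**2. Two readings of the base.**
- *Existing activity is stripped out.* The comparator is then a hypothetical one, and cases that the programme already finds can be credited to a new strategy.
- *Existing activity stays in through calibration.* The description is then wrong and some active detection is treated as passive, but the increment need not be inflated.

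The text does not say which applies.

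**3. What stripping could do to impact.** The article gives no impact or ICER figure to reproduce. Its Introduction gives 213 MDR-TB cases detected in 2020 out of about 800 estimated per year (213/800 = 26.6%). It does not say how many of the 213 were found actively. The following are therefore assumptions:
- f: share of the 213 found by existing activity, so A = 213f
- D: annual detections when a strategy is added to current practice, so the true gain is t = D − 213
- o: share of A that the new strategy would also find

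The gain against the stripped base is t + oA. With D = 300, t = 87:

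| f | A | gain, o = 0 | gain, o = 0.5 | gain, o = 1 | ratio to 87, o = 1 |
|---|---|---|---|---|---|
| 0% | 0 | 87 | 87 | 87 | 1.00 |
| 5% | 10.65 | 87 | 92.3 | 97.7 | 1.12 |
| 10% | 21.3 | 87 | 97.7 | 108.3 | 1.24 |
| 20% | 42.6 | 87 | 108.3 | 129.6 | 1.49 |
| 30% | 63.9 | 87 | 119.0 | 150.9 | 1.73 |

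With complete overlap (o = 1), D from 250 to 400 and f from 5% to 30%, the ratio runs from 1.06 (197.65/187) to 2.73 (100.9/37). With f = 0 or o = 0 it is 1.

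**4. What stripping could do to cost per additional detection.**
- *Strategy added to existing activity, at unchanged cost.* The figure against the stripped base, divided by the figure against current practice, is t/(t + oA). At D = 300 and f = 10% this is 87/108.3 = 0.80 for o = 1, 87/97.65 = 0.89 for o = 0.5, and 1 for o = 0. With o = 1, over the ranges in step 3, it runs from 0.37 to 0.95.
- *Strategy replaces existing activity, with D the total after replacement.* The gain against the stripped base is b = D − 213(1 − f) = 108.3 at f = 10%. Here the two gains differ by the whole of A, whatever the overlap. Let the strategy cost 1 unit per case found beyond passive detection, and existing activity k units per case. The ratio is t/(b − kA):
  - k = 0.25: 87/102.975 = 0.84
  - k = 0.5: 87/97.65 = 0.89
  - k = 1: 87/87 = 1.00
  - k = 2: 87/65.7 = 1.32

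The direction therefore depends on add-on versus replacement and on relative cost, neither of which the article states.

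**The case against.** The evidence on current activity is thin. Participant identification mentions the programme's active case finding only as a fallback source of participants, without scale, region, yield or an MDR-TB focus. The Introduction's sentence reports difficulties, not coverage. If the active yield of MDR-TB is near zero, a base without it is a fair approximation. Calibration may also keep existing finds in the base. The article condenses a fuller plan, the model is still to be built, and wide sensitivity analyses are promised. All of this limits the size and certainty of the effect. It does not remove the contradiction: the comparator is stated as a rule, not left to another document, and no analysis with a different comparator is stated.

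Three stronger readings are tempting, and the document does not support them.
- A reader might infer that the results are certainly biased in favour of the new strategies. That holds only if existing activity is stripped out; even then, dropping its costs can move the ICER the other way (step 4).
- A reader might infer that household contact screening gains most. Nothing shown says that the programme's active case finding covers household contacts.
- A reader might put a figure on the error. For example, with f of 5% to 20% and a true gain of 50, 50/60.65 = 0.82 and 50/92.6 = 0.54, so cost per additional case looks 18% to 46% too low. That assumes the share, the gain, complete overlap and unchanged cost. It also concerns cost per detection, whereas the primary outcome is a lifetime ICER from the societal perspective.

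**Conclusion.** The concern holds as an inconsistency in the stated comparator. The base cannot be both the status quo and free of active case finding when the article itself draws on the programme's active case finding. As written, neither the impact estimates nor the primary ICER can be read as increments over current practice.

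If existing activity is stripped from the base, impact is probably overstated: for an added strategy, to the extent that it finds the same cases. The ICER may look too favourable or too unfavourable. The size cannot be derived from the document. The ratios above only illustrate how it depends on assumed shares, overlap and costs, and they do not transfer directly to the lifetime ICER. The effect is negligible if the programme's active MDR-TB yield is near zero.

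**What to change.** In Epidemiological modelling, define the base as current practice: passive detection plus the programme's existing active case finding at its current coverage, yield and cost, calibrated to observed detection. State for each of the three strategies whether it adds to or replaces that activity, and carry the costs accordingly. Say in Health economic modelling that the ICER uses this base. Keep the scenario without active case finding only as a labelled secondary analysis.

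The cost is a change of wording and a request to the national programme, which already collaborates on the protocol, for its current coverage, yield and cost data. Enrolment and data collection from participants are unaffected. The downside is that the ICERs may be less favourable.

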#### Health economic modelling

During the feasibility studies, costing data will be collected from each site in a standardised way. Decision analysis will be carried out using the ICER tool. The primary outcome will be the ICER, comparing the three case finding strategies with the baseline scenario, from the societal perspective over a lifetime analytical horizon. One-way sensitivity analyses will be conducted on all model parameters, multiway sensitivity analyses on parameters most critical to the cost-effectiveness estimate, and a probabilistic uncertainty analysis where all parameters are varied simultaneously over distributions to construct 95% uncertainty ranges and cost-effectiveness acceptability curves.

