#### Participant identification

For the feasibility study, participants will be enrolled from three zones, namely (a) transmission hotspots, (b) household and other close contacts of MDR-TB cases identified by the TB programme, and (c) visitors to patients with MDR-TB admitted to TB wards in hospitals. A sample size calculation is not indicated since one of the goals of feasibility studies is to inform on sample size calculations for the planning of large-scale appropriately powered intervention studies.^10 11^ A sample size of 600 participants for each intervention strategy will inform on the feasibility and acceptability of the interventions, the yield and the cost per additional case.

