#### Data collection

There will be both qualitative and quantitative components of this objective. For the qualitative component, pre-intervention in-depth qualitative data will be collected from three groups of participants (healthcare workers, N=~9; community members, N=~9; patients, N=~12; total N=~30) in each of the regions. A semistructured discussion guide will include discussion questions and participatory activities to elicit knowledge, beliefs and attitudes regarding MDR-TB, and acceptability of the proposed study methodology. This information will be used to inform the design and implementation of the quantitative component of the feasibility study. For the quantitative component, a scoping review on MDR-TB case finding interventions will be conducted to document case finding intervention strategies for MDR-TB in LMICs. The first intervention strategy of the feasibility study, focusing on transmission hotspots, will be tailored to the local context.^12^ For the second intervention strategy of the feasibility study, focusing on household and other contacts, MDR-TB household contact studies from Peru will be used as examples.^13 14^ Peru has a similar TB burden to Namibia, is also an LMIC and has conducted similar case finding studies which serve as good examples for this type of work; we therefore refer to the Peruvian studies as comparison. For the third intervention strategy of the feasibility study, focusing on the TB wards, all consecutive visitors of patients with MDR-TB will be asked to participate (N=~600). We are unaware of similar work of this nature and therefore cannot add comparative data for this strategy.

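### The primary economic outcome compares each strategy only with a no-active-case-finding baseline, which cannot support a choice between the three strategies or a combination of them

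*Protocol article*

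**What the plan says.** Under Objective 3, Health economic modelling, the protocol article fixes the comparison: "The primary outcome will be the ICER, comparing the three case finding strategies with the baseline scenario". The perspective is societal and the horizon is lifetime. One-way, multiway and probabilistic sensitivity analyses and acceptability curves follow. These vary parameters; no change of comparator is mentioned.

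Under Objective 3, Epidemiological modelling, the baseline is defined: "In a base scenario, the status quo will be evaluated, assuming no active case finding". The effect measure follows: "Each of the three interventions will then be evaluated and their impact determined though divergence from the base". Neither section names a comparison of one strategy with another, a dominance check or a combined scenario.

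Under Objective 2, Data management and analysis, one ratio per strategy is planned: "Cost will be determined using the incremental cost-effectiveness ratio (ICER) for each case finding intervention strategy".

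Under Objective 2, Participant identification, zone (a) is transmission hotspots, zone (b) is "household and other close contacts of MDR-TB cases identified by the TB programme" and zone (c) is "visitors to patients with MDR-TB admitted to TB wards in hospitals". Nothing makes the zones mutually exclusive. For zone (c), Objective 2, Data collection, adds that "all consecutive visitors of patients with MDR-TB will be asked to participate (N=~600").

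The Discussion expects the findings to help decide where programme resources go, with hotspot areas as the example, and to guide national programme policy.

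**The concern.** A ratio against doing nothing answers whether a programme is worth running by itself. It does not answer which of several programmes to run, or whether to add a second to a first.

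- **If the strategies are alternatives**, each should be compared with the next less costly option that is not dominated. A costlier strategy can look acceptable against baseline while its extra benefit over a cheaper one is poor value.
- **If the strategies are run together**, a ward visitor may also be a household or close contact of a case, and either may belong to a hotspot. Part of the second strategy's standalone benefit may then already have been obtained by the first.

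A programme that reads the three primary ratios as a priority list could fund the options in the wrong order or expect more joint benefit than it will get.

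**Working it through.** The documents give no ratio, cost, effect or overlap share, so there is no planned figure to reproduce. The values below are **assumed**, in arbitrary units, and serve only to show how the planned comparison behaves.

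**Assumed cost C and benefit E against baseline:** household C = 100, E = 1.0; hospital C = 60, E = 0.5; hotspot C = 300, E = 2.0.

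**Step 1: the planned ratios, C/E.** Household 100/1.0 = 100; hospital 60/0.5 = 120; hotspot 300/2.0 = 150.

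**Step 2: independent and additive.** Enumerate the combinations and move along the frontier:
- household alone: 100/1.0 = 100
- adding hospital: (160 − 100)/(1.5 − 1.0) = 120
- adding hotspot: (460 − 160)/(3.5 − 1.5) = 150

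These equal Step 1, so in this case the baseline ratios suffice.

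**Step 3: alternatives, only one to be funded; no overlap needed.** Order by cost: hospital, household, hotspot.
- hospital against baseline: 120
- household against hospital: (100 − 60)/(1.0 − 0.5) = 80

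Since 80 is below 120, hospital is extendedly dominated and is removed.
- household against baseline: 100
- hotspot against household: (300 − 100)/(2.0 − 1.0) = 200, not 150

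For any threshold between 150 and 200, hotspot passes against baseline although household has the larger net benefit. At 175, for example, household gives 175 × 1.0 − 100 = 75 and hotspot gives 175 × 2.0 − 300 = 50.

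**Step 4: hospital added to household, with overlap.** Let o be the share of the hospital benefit that household screening already obtains, with the hospital cost still paid in full. The add-on ratio is 60/(0.5 × (1 − o)). Adding the two separate benefits overstates the joint benefit by 1.5/(1 + 0.5 × (1 − o)) − 1.

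| o | Hospital add-on ratio | Overstatement if benefits are added |
|---|---|---|
| 0 | 120 | 0% |
| 0.10 | 133 | 3.4% |
| 0.25 | 160 | 9.1% |
| 0.50 | 240 | 20% |
| 0.75 | 480 | 33% |

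**Step 5: order of hospital and hotspot once household is funded.** With no hotspot overlap, hospital passes 150 when 120/(1 − o) > 150, that is o > 0.20. If hotspot screening also duplicates a share p of the household benefit, its add-on ratio is 300/(2 − p). With p = o, the order reverses only when 120/(1 − o) > 300/(2 − o), that is o > 1/3. The reversal point therefore depends on assumptions that the documents cannot settle.

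**Step 6: the full-cost assumption.** If overlap also saves a share c of the hospital cost, the add-on ratio is 120 × (1 − c)/(1 − o). With c = o it stays at 120; with o = 0.50 and c = 0.25 it is 180. The baseline ratio understates the add-on ratio whenever benefit falls by more than cost.

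**The case against.** The strongest reply has four parts.

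1. **The plan does not rank or add.** Each intervention is a separate scenario, and a case that two routes could find properly counts in each. This stands. A reader might infer that the plan double-counts cases; it does not, because it sums nothing. The error would come from later use of the ratios.
2. **The next-best-comparator rule is for mutually exclusive options.** This stands too. Contact, visitor and hotspot screening can run together, and for independent programmes a baseline comparison is adequate (Step 2). Enumerating the combinations makes the options mutually exclusive, so the rule then applies.
3. **The overlap is not documented.** This stands as to size. A reader might infer that visitors are mostly contacts already; no passage says so. Nor need hotspots be where contacts live, since they are built from shared spaces and social networks as well as homes. What remains is that the zone definitions permit overlap and plan no estimate of it. A reader might also infer that the number needed to screen depends on enrolment order. The documents do not show this: all consecutive visitors are invited, and no rule credits contacts to zone (b) alone.
4. **Frontier methods belong in an analysis plan, and naming a baseline does not forbid further comparisons.** The second half is fair: the full protocol may contain an incremental analysis. But the article does not leave the comparator open. It states it for the primary economic outcome, and the modelling section repeats it.

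**Conclusion.** The concern holds in a limited form. The article fixes baseline-only ratios as the primary economic outcome. They are adequate only if the strategies are independent and additive, which the zone definitions do not ensure. As alternatives, the ratios do not show dominance or extended dominance; as components of a package, they can understate the cost per added unit of benefit.

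The size and direction of any change in ranking cannot be determined from the documents. The changes shown (150 to 200, and 120 to between 133 and 480) rest on assumed costs and benefits, overlap of 10% to 75% and, for the second, full payment of the added strategy's cost. The ratios against baseline are not wrong in themselves. They are insufficient for the resource allocation that the Discussion has in view.

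**What to change.** Keep the three baseline ratios and add a full incremental analysis:

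- Model the baseline, the three single strategies and their four combinations (2 × 2 × 2 = 8 options).
- Order them by cost, remove dominated and extendedly dominated options, and report each ratio against the next best remaining option.
- Show acceptability curves for all options jointly, for example through net monetary benefit, from the probabilistic analysis already planned.
- Record at enrolment every zone for which a participant qualifies, so that overlap can be estimated and used in the combined scenarios.
- Report visitor yield overall and among visitors who are not already contacts of a known case.

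The cost is one field on the enrolment form and extra runs of the same model. The field is best added while recruitment is open, because zone membership may be hard to reconstruct later.
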